#### Quality of life

Quality of life is measured using the Australian Quality of Life Survey (AQoL-8D) consisting of eight dimensions (Independent Living, Happiness, Mental Health, Coping, Relationships, Self Worth, Pain, Senses) totaling 35 items [104] . The questionnaire is validated and has high test-retest reliability [105].

#### Motivation for physical activity and motivation to break up sedentary behaviour

Motivation for physical activity and motivation to break up sedentary behaviour are assessed using two separate modified versions of the validated Behavioural Regulation Exercise Questionnaire (BREQ-3) [106] based on self-determination theory [107]. The original prompt of “Why do you engage in exercise?” has been modified for the two questionnaires separately as “Why do you engage or not engage in physical activity?” and “Why do you break up sitting with standing up and/or moving more versus continued sitting?” respectively. These two questionnaires contain 24 items each with a five-point Likert scale. There are six subscales that represent the average scores for 4 items: amotivation (lack of intention), four subscales reflecting degrees of extrinsic motivation - external regulation, introjected regulation, identified regulation, integrated regulation - and intrinsic regulation. This is the first known study to measure motivation to break up sitting time using a modified version of the BREQ-3 questionnaire.

#### Menopause status questionnaire

The menopause status questionnaire asks questions to assist in classifying menopause status according to the Stages of Reproductive Aging Workshop (STRAW+ 10) criteria [108]. It is administered only to those participants identifying as female. Participants answer questions pertaining to criteria that fall outside of the STRAW+ 10 including polycystic ovarian syndrome, premature ovarian failure, hypothalamic amenorrhea, oestrogenic malignancy, or endrometriosis. To determine menopause status, participants are asked when (if at all) they had their first menstrual period, and whether they have either temporarily stopped, or finished having their period. Menstrual cycle history, use of hormonal contraceptive or hormonal therapy, and associated symptoms (according to Greene Clinimetric scale) [109] are recorded.

#### Experience in the OPTIMISE your health intervention

At the 6, and 12 month assessments for the intervention group, and at the 18 month assessment for the delayed intervention group, questions are included pertaining to the participants’ experience in the intervention. These questions are primarily adapted from previous research [110] and related to overall experience, as well as experience with the specific components of the intervention. Participants are asked about how the intervention has led to changes in their activities of daily living, and whether the trial changed these activities on a scale of a lot, a little, or no change. The components of the trial are ranked from most important to least important according to their perceived utility to assist with making changes in the domains of sitting less and moving more. Finally, participants are asked about their goal setting, and whether it was realistic and achievable and supported by the research team, as well as the applicability of the intervention to people without diabetes in order to inform the generalisability of the intervention messaging.

#### COVID-19 impact questionnaires

A questionnaire was originally added to assess the immediate impact of the pandemic and restrictions (Additional file 8). The questionnaire records any changes that the participant incurred with respect to workload, work environment, caring responsibilities, sitting and standing at their workstation, joint and muscle discomfort, motivations to sit less and move more, and physical activity participation changes due to the pandemic and restrictions. Following the temporary ending of restrictions and return of the trial in October 2020, this questionnaire was replaced with a five-item questionnaire. The new questionnaire asks on a ten point scale (not at all – very much) how the pandemic impacts self-management of diabetes, sitting at desired levels, moving at desired levels, and participation in the trial. Finally, participants are asked how the pandemic has changed their work commute.

### Adverse events

Any adverse events encountered during the trial are recorded by the research staff when they arise. Adverse health events may lead to a pause in participation or withdrawal from the study. Information collected includes the type of adverse event, the date of onset and resolution (if applicable), the maximum intensity of the adverse event (mild, moderate, severe), action taken, the adjusted medication due to event, the likelihood of relationship to the trial (scale of 1–4; 1 indicating unrelated; 4 indicating definitely related), and whether the event has resolved. Adverse events are reported to Baker Governance and Alfred Ethics Committee (Additional file 10). The participant that reports the adverse event is followed up with a phone call in order to monitor their health and participation in the trial.

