**Methods:**

This is a two-arm RCT being conducted in Melbourne, Australia. Desk-based workers (≥0.8 full-time equivalent) aged 35–65 years, ambulatory, and with T2D and managed glycaemic control (6.5–10.0% HbA1c), are randomised to the multicomponent intervention (target *n* = 125) or delayed-intervention control (target *n* = 125) conditions. All intervention participants receive 6 months of tailored health coaching assisting them to “sit less” and “move more” at work and throughout the day, supported by a sit-stand desktop workstation and an activity tracker (Fitbit). Participants receive text message-based extended care for a further 6-months (6–12 months) followed by 6-months of non-contact (12–18 months: maintenance). Delayed intervention occurs at 12–18 months for the control arm. Assessments are undertaken at baseline, 3, 6, 12, 15 and 18-months. Primary outcomes are activPAL-measured sitting time (h/16 h day), glycosylated haemoglobin (HbA1c; %, mmol/mol) and, cognitive function measures (visual learning and new memory; Paired Associates Learning Total Errors [adjusted]). Secondary, exploratory, and process outcomes will also be collected throughout the trial.

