#### Face-to-face and telephone health coaching (0–6 months)

The individual health coaching component targets the Behaviour Change Wheel intervention functions of persuasion, education and training. Health coaches, all of whom have at least a bachelor level of training in exercise physiology, nutrition, or nursing, are trained in the delivery of the intervention, including motivational interviewing techniques [40]. A written script is maintained for intervention fidelity and consistency of delivery. Key aims of the health coaching are to build rapport, provide education about the importance of reducing sedentary behaviour and increasing movement throughout the day, encourage sustained self-management, and goal setting. In conjunction with the first health coaching session, participants are provided with an intervention handbook, containing written educational information and instructions (Additional file 4), an email containing basic tips to reduce sitting, a 2-min educational video describing the link between diabetes and sitting and activity levels, a video demonstrating how to perform the simple resistance activity breaks, and an activity feedback report (Additional file 5) generated from their most recent ten days of activity monitor (activPAL) wear. The health coaching consists of ten sessions (two in-person and eight via telephone; approximately 15–30 min in duration) over 6 months. Health coaches follow standardised outlines for each session set out in REDCap forms containing both the coaching script and embedded data-collection fields to further enhance intervention fidelity and collect data for process evaluation. The data collection is also used to guide subsequent health coaching sessions (e.g., goals, goal attainment). All health coaching sessions are delivered by the same health coach wherever possible and conducted at a time selected by the participant.

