#### Sessions 2–6, 8–10 (telephone)

The seven telephone-delivered sessions occur on a tapered schedule: one call per week for the first three weeks reducing to one call every three weeks for the remaining 23 weeks (approximate timeframe). Each session lasts for a duration of 15 to 30 min. The sessions are designed to check on the participant’s progress (both subjectively and objectively with their Fitbit data as in Fig. 2), address problems with adherence, revise goals as needed, and reinforce goal attainment. Adoption of new strategies, and the progression of goals is encouraged by health coaches when participants report high engagement and success with their current plan.

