#### Extended care (tailored text messaging; 6–12 months; expanded protocol) – OPTIMISE

The 6–12 month intervention phase is designed to support maintained behaviour change (or continued improvement) after the 10-session intensive phase has been completed. This program, which is administered remotely, transitions participants from the face-to-face and telephone delivered health coaching to a tailored text message service using the web-based semi-automated platform, propelo™ (www.propelo.com.au). Coaching involves 24 weeks of text message contact and one telephone coaching session (midway) with their health coach.

The text message content has been informed from formative discussion with research staff, health coaches, and completed OPTIMISE intervention participants who were recruited before the expanded protocol was initiated. This formative research involved qualitative interviews and user-testing of draft text content. Key findings from this formative work highlighted the need for the text message program to: use supportive, non-judgemental language; continue to leverage off the rapport established between the health coach and participant during the intensive phase; and, ensure the texts are tailored to the participant’s Fitbit data. The texts target three key behaviour change strategies in three different types of text messages (see Table 1): prompt actions in real-time (via ‘Sit less prompts’ and ‘Move More promps’); promote ongoing self-monitoring of behaviour (via ‘Check-ins’); and, monitor and reward goal attainment (via ‘Check-ins’).

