### Control – delayed intervention

To minimise attrition prior to receiving their delayed intervention (at 12 months), the control participants receive contact in the form of a thank-you letter commencing two weeks after the baseline assessment then, monthly emails containing diabetes fact sheets, along with a follow-up phone call (verifying they received the fact sheet and enquiring whether they have any questions). The fact sheets are published by the NDSS, and provide a non-tailored diabetes-management advice. The fact sheets do not cover sedentary behaviour. Participants may seek other lifestyle interventions to manage their diabetes during this period. Following the completion of the 12 month assessment, control participants are provided with a modified version of the intervention (12–18 months). In the original protocol, delayed intervention (6–9 months) participants were provided with a sit-stand workstation and written education materials only. In the expanded protocol this is referred to as OPTIMISED (12–18 months). As with OPTIMISE, OPTIMISED includes environmental support via a sit-stand workstation, provision of a Fitbit, and health behaviour change coaching (one delivered by online video teleconferencing and two delivered by telephone). However, the behaviour change health coaching and educational materials are modified to be more suitable for scale-up and external delivery, based on consultation and collaboration with end users and stakeholders. The intervention adaptation process, and the resultant OPTIMISED intervention protocol, will be reported elsewhere.

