^b^ Dropped during COVID restrictions

^c^ Added part way through study

^d^ Subsample only - recruited first 30 participants, completed before expanded protocol began

^e^ Not timed with the assessments but triggered by events: soon after the Australian government implemented restrictions March 2020 (COVID-19 pandemic restrictions) or upon reporting of a withdrawal or adverse event

^f^ When reported

**Table 3 Tab3:** Clinical and device-based measures collected in the in-person visit clinical assessments

Component	Key constructs	Measures	
		Primary / secondary outcomes	Other measures
Fasting blood draws	Glycaemic control	Glycosylated haemoglobin (HbA1c %, HbA1c mmol/mol)*	
	Fasting glucose metabolism	Glucose and Insulin	
	Fasting lipid metabolism	LDL, HDL, Total cholesterol, Triglycerides	
	Inflammatory markers	Hs-CRP, TNF-α, IL-6, IL-1B, Adiponectin, Leptin	IFNy, IL-10, IL-12, IL-8, IL-4
	Neurotrophic factors	BDNF, IGF-1	NGF, VEGF-A
	Genetic risk factors		ApoE4
2 h Oral Glucose Tolerance Test	Postprandial metabolism of glucose & insulin	iAUC glucose, iAUC insulin, 2 h post-prandial glucose, 2 h post-prandial insulin	
Anthropometric	Body weight & body composition	Weight, waist circumference, DXA assessed total and regional fat mass, lean mass, total body fat percentage, DXA software estimated visceral adipose tissue mass	Height, BMI
Vascular	Blood pressure & heart rate	Resting systolic blood pressure, diastolic blood pressure, mean arterial pressure	Resting heart rate
	Flow Mediated Dilation	Post-deflation peak vessel diameter compared to resting diameter (FMD%)	Shear rate (cm/s), Shear rate AUC
Cambridge Neuropsychological Test Automated Battery (CANTAB)	Visual learning and new memory	Paired Associates Learning total errors (adjusted)^b^ (PAL TEA), PAL total errors 12 shapes (adjusted)	PAL total errors, PAL total errors 12 patterns
	Reaction Time	Reaction Time (RTI) simple median reaction time, RTI simple median movement time & RTI median 5-choice reaction time, RTI median 5-choice movement time	RTI simple error score (all), RTI total error score (5-choice)
	Visual matching ability and visual recognition memory	Delayed Matching to Sample (DMS) percent correct, DMS median correct latency	DMS total errors, DMS total correct (12 s delay)
	Working memory	Spatial Working Memory (SWM) between errors, SWM between errors (12 boxes), SWM strategy (6–12 boxes)	SWM total errors, SWM total errors (12 boxes)

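### Adverse event capture is triggered by reports while scheduled contact differs by arm and phase, so event counts by arm over months 0–12 may partly reflect opportunity to report

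*Protocol article*

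**What the plan says.** The Adverse events section states the capture rule: "Any adverse events encountered during the trial are recorded by the research staff when they arise". It then treats the participant as the source of the report: "The participant that reports the adverse event is followed up with a phone call". In Table 2 (Data collection) the withdrawal and adverse events log is ticked at all six timepoints, but footnote f qualifies those ticks as "When reported". The article describes no adverse event question asked at fixed times and in the same way in both arms. Study design and randomisation says that neither participants nor assessors can be blinded.

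Scheduled contact is set out elsewhere:

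- Intervention arm, months 0–6: "The health coaching consists of ten sessions (two in-person and eight via telephone; approximately 15–30 min in duration) over 6 months".
- Intervention arm, months 6–12: "Coaching involves 24 weeks of text message contact and one telephone coaching session (midway) with their health coach".
- Control arm, to month 12: "monthly emails containing diabetes fact sheets, along with a follow-up phone call (verifying they received the fact sheet and enquiring whether they have any questions".
- Both arms: clinic visits at 3, 6, 12 and 18 months after baseline (Clinical assessment).

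**The concern.** When an event enters the log because someone reports it, the chance of its being logged depends partly on how often the participant speaks to staff. Here that frequency is set by the arm. The intervention arm has more contact during intensive coaching. On the natural reading of the control procedure, it has much less once coaching gives way to text messages, although participants are still using the workstation and pursuing their activity goals.

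A table of adverse events by arm drawn from this log would then mix true risk with opportunity to report. This matters because the article itself says, under Intervention targets, that too much standing as well as too much sitting may do harm. A reassuring or worrying difference in counts could not be taken at face value.

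**Working it through.** **1. The article's own contact total.** Two in-person plus eight telephone sessions give 2 + 8 = 10. This agrees with the ten contacts stated under Intervention protocol and core components. One passage conflicts: "The seven telephone-delivered sessions occur on a tapered schedule". On that wording the total is 2 + 7 = 9. The heading of the same section lists sessions 2–6 and 8–10, which is 5 + 3 = 8 telephone sessions, so 10 is used below.

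**2. Other inputs.**
- Control calls: about 6 per six months. This assumes one call for each monthly fact sheet, which the text does not say explicitly.
- Intervention calls in months 6–12: 1.
- Common clinic visits: 2 in months 0–6 (at 3 and 6 months) and 1 in months 6–12 (at 12 months).
- Overlap: coaching session 7 is scheduled to coincide with the 3-month visit, so 1 is subtracted in the intervention arm.

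**3. Count.** Live contacts = arm-specific contacts + common visits − overlap.

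| Phase | Intervention | Control |
|---|---|---|
| Months 0–6 | 10 + 2 − 1 = 11 | 6 + 2 = 8 |
| Months 6–12 | 1 + 1 = 2 | 6 + 1 = 7 |
| Months 0–12 | 13 | 15 |

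**4. Sensitivity to the reading of the text.**
- Seven telephone sessions: months 0–6 become 10 v 8.
- Five control calls in the first phase: months 0–6 become 11 v 7.
- A single control call in all, placed in the first phase: 11 v (1 + 2) = 11 v 3, then 2 v (0 + 1) = 2 v 1. The deficit in months 6–12 disappears and the imbalance in months 0–6 grows.
- COVID restrictions, when clinic visits are replaced by emailed questionnaires and off-site HbA1c testing: 10 v 6, then 1 v 6.

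**5. Direction only.** Suppose each contact in a phase independently picks up an event with probability q. Capture over m contacts is 1 − (1 − q)^m.
- q = 0.1, months 0–6: 1 − 0.9^11 = 0.69 v 1 − 0.9^8 = 0.57.
- q = 0.1, months 6–12: 1 − 0.9^2 = 0.19 v 1 − 0.9^7 = 0.52.
- q = 0.5: 1.00 v 1.00, then 0.75 v 0.99.
- Single control call, q = 0.1, months 6–12: 0.19 v 1 − 0.9^1 = 0.10, which is the opposite direction.

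The value of q has no source in the document, and the model lets every contact in a phase serve every event in it. It shows that the sign can differ between phases and between readings. It does not estimate a bias.

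**6. Does other data collection close the gap?** Medication changes and allied health appointments are recorded at the clinic assessments in both arms, and the health history checklist is updated when something changes. The surveys cover fatigue and illness leave. The musculoskeletal questionnaire looks back 3 months and 7 days; given at 12 months, it leaves roughly months 6–9 uncovered, and no assessment falls between 6 and 12 months. None of these instruments is said to feed the adverse event log.

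**The case against.** The strongest reply is that this is a condensed article. It does not say that staff refrain from asking, the log is ticked at every timepoint, and Additional file 10, cited in the Adverse events section, is not shown. A reader might infer that events are logged only if volunteered; the text does not go that far. What stands is that the article does state a rule, and that rule is triggered by a report rather than by a schedule.

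Second, Statistical analyses specifies no comparison of adverse events between arms, and adverse events are not listed among the outcomes. That is correct, so no planned test is shown to be biased. Any tabulation of the log by arm would still carry the problem.

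Third, the imbalance is softened. Total contacts over months 0–12 are close (13 v 15), and intervention participants receive at least weekly texts and can reply. Control calls only confirm receipt of a fact sheet and invite questions, and both arms give the same medication, musculoskeletal and fatigue data. All of this reduces the concern. It does not remove it, because similar totals conceal opposite imbalances in the two phases and nothing links these sources to the log.

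Fourth, months 12–18 might be read as further evidence, since contact with the common visit is then 0 + 1 = 1 v 3 + 1 = 4. That phase has no bearing on the comparison with usual care, because controls are by then receiving OPTIMISED and the planned analyses are within group.

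**Conclusion.** The point holds as a weakness in the stated capture rule that is cheap to repair, not as a demonstrated bias. In an unblinded trial, report-triggered capture combined with contacts of about 11 v 8 and then 2 v 7 means that event counts by arm over months 0–12 may partly reflect opportunity to report. The second pair depends on one control call per monthly fact sheet, and on the expanded protocol: the 27 participants of the original iteration completed only the 6-month version.

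A reader might go further and conclude that the intervention arm's events will be under-recorded after month 6, or might attach a rate ratio to it. For example, suppose that an event is logged only if a contact follows within w weeks, and that coverage of a 26-week phase is contacts × w / 26, capped at 1. With 2 v 7 contacts and equal true rates, the ratio is (8/26)/1 = 0.31 for w = 4 and (24/26)/1 = 0.92 for w = 12. The documents give no basis for any w, text replies are ignored, and the direction fails if only one control call was meant. The bias could run either way, and its size cannot be determined from the document.

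**What to change.** - Add one fixed adverse event question, covering the time since the last assessment and worded identically for both arms, to the OPTIMISE survey. Table 2 already schedules that survey at 3, 6, 12, 15 and 18 months. It has a self-completion alternative under COVID restrictions, so the question would survive the loss of clinic visits.
- Change Table 2 footnote f to: asked at each assessment and when reported.
- Base any between-arm adverse event summary on the scheduled question, over months 0–6 and 0–12. List events reported between assessments separately, by arm.
- State whether each monthly fact sheet has its own follow-up call, and reconcile the count of seven telephone sessions with the eight given elsewhere.

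The cost is one survey item and a sentence or two in the protocol. The downsides are more minor events to log, and recall of up to 6 months at the 12-month assessment.

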### Process evaluation

A process evaluation is undertaken for the intervention and its components by assessing direct implementation indicators and surveying participants at the end of the intensive (6 months) and extended phase (12 months) timepoints for the intervention group and at 18 months for the delayed intervention group. Elements of context (e.g. workplace support), implementation (e.g., number and duration of health coaching sessions), and mechanisms of impact (including potential mediators) are explored in accordance with the Medical Research Council process evaluation framework [111]. Process evaluation for the intervention components is summarised in Table 5.

**Table 5 Tab5:** Data collected in OPTIMISE Your Health intervention participants for process evaluation

Component	Data collected	Collected
Health coaching: participation and selections	Danger zones for sitting	Sessions 1 & 7
	Strategies to sit less at work selected by participant (select any number of 12 listed + 2 ‘other’)	Sessions 1–10
	Strategies to sit move more at work selected by participant (select any number 17 listed + 2 ‘other’)	Sessions 1–10
	Strategies to sit less across the day selected by participant (select any number 12 listed + 2 ‘other’	Sessions 1–10
	Strategies to move across the day selected / continued (select any number 8 listed + 2 ‘other’)	Sessions 1–10
	Goal setting - smart goals (sit less across the day, sit less at work, move more at work, move more across the day)	Sessions 1–10
	Stand more at desk goal	Sessions 1–10
	Active breaks goal (encouraged 1 break per hour)	Sessions 1–10
	Daily steps goal	Sessions 1–10
	Readiness level (1–10) to change sitting and moving habits	Sessions 1 & 7
	Anticipated barriers to goal achievement	Sessions 1–10
	General review of strategies / goals (open text) including barriers, ease/difficulty & modifications	Sessions 2–10
	Number of coaching sessions completed (0–2 face to face; 0–8 telephone)	Sessions 1–10
OPTIMISE-extended health coaching: participation and selections	Two danger zones for sitting (1 & 2) selected by coach from 3 listed + other^a^	Tailoring session 1 & 2
	One strategy to sit less per danger zone selected by coach from 32 listed + other^a^	Tailoring session 1 & 2
	Two strategies to move more (1 & 2) selected by coach from 17 listed and other^a^	Tailoring session 1 & 2
	Active breaks goal set by participant (n active breaks/ day, 1–24)	Session 10 & Tailoring 2
	Daily steps goal set by participant (n steps / day, 5000–20,000)	Session 10 & Tailoring 2
	Number of texts sent (total, by week, by type), number of text messages replied to by participants (total, by week), content of participant replies.	propelo
Fitbit (Fitabase)	Usage (wear days, non-wear days)	Continuous from Session 1 to end of study
	Physical activity / sedentary behaviour (step counts, estimated energy expenditure, time spent in LPA, MPA, VPA, inctive behaviour), physical activity events autodetected & logged (e.g., ‘weights’, ‘walk’)	
	Heart rate	
	Sleep & sleep quality (Total sleep time duration, duration of each sleep stage, sleep onset latency, sleep efficiency, number and duration of wakes after sleep onset, restlessness count and durations)	
Intervention fidelity	Health coaching participation (n sessions completed)	Sessions 1–10
	Extended care participation (n text messages received)	Propelo
	Fitbit usage (% of days in intervention wore Fitbit)	Fitbit
	Sit-stand workstation in standing postion (not used / some days / most days / every day)	OPTIMISE survey 6 M & 12 M
COVID-19	Impact of COVID-19 pandemic on abilty to participate in OPTIMISE program (0–10); 1 item	OPTIMISE survey 6 M, 12 M & 18 M
Intervention satisfaction	Overall satisfaction (1–10) with the OPTIMISE intervention / the text message health coaching: satisfaction level, whether would recommend, usefulness (3 items)	OPTIMISE survey 6 M & 12 M
	Rating of each intervention element (1–10) over last 6 months: coaching (4 items; 6 M); text message coaching (4 items; 12 M); feedback (7 items); sit-stand workstation (10 items); Fitbit (10 items); goal setting (4 items).	OPTIMISE survey 6 M & 12 M
	Appropriateness of text message frequency, from 1 (nowhere near enough) to 10 (far too many) with 5 = the right amount (1 item)	OPTIMISE survey 12 M
	Likes & suggestions for improvement (open text) re: the OPTIMISE intervention / the text message health coaching	OPTIMISE survey 6 M & 12 M
	Usefulness (1–10) over the last 6 months for behavior change, for sitting less and for moving more of the intervention elements: face to face coaching (6 M); telephone coaching (6 M); text message coaching (12 M); monitoring steps/sitting via coach feedback; goal setting; sit-stand workstation; Fitbit.	OPTIMISE survey 6 M & 12 M

^a^ Health coach selects based on participant’s prior selections at tailoring session 1 and then participant can revised at tailoring session 2

